**Fig. 1 Fig1:**
[figure not shown]
Summary of the three sub-studies which form the Switching Study programme

### Inclusion criteria

All patients with a TTR <50 % prescribed warfarin therapy (for recruitment to group 2 and group 3). Where the low TTR is not due recent hospital admissions, surgical procedures or significant drug changes; this will be determined, following initial identification of patients in this group.

A control group will also be recruited comprising of patients with a TTR >75 % (for recruitment to group 1).

### Exclusion criteria

Patients with a TTR >50–<75 % (for recruitment to group 2 and group 3).

Patients with a contra-indication to NOAC (i.e. abnormal liver function tests, CrCl <15 ml/min, taking concurrent interacting drugs which are contra-indicated).

Those patients unable to attend clinic for a formal consultation.

Those patients unable to read English.

Those patients who do not wish to participate.

Pregnant patients.

### Study outcomes

Individual % medication adherence to direct acting anticoagulant therapy (1 year following switch)Changes in patients beliefs about the anticoagulation therapy prescribed, at 1 month and 1 year following a switch to NOAC therapyChanges in patients illness perceptions (1 month and 1 year following switch)Changes in patients anticoagulation specific quality of life (1 month and 1 year following switch)Persistence with NOAC therapy, following a switch from VKA (1 year following switch)

### Data collection

Table 1 outlines the study visit schedule and what instruments will be administered when for study II, including details of clinical information collected for patients who consent to the study. For study III, a new group of patients will be recruited, with the study visit schedule also following the schedule outlined in Table 1.

**Table 1 Tab1:** Schedule of visits for patients recruited to studies II and III

*Visit 1 (baseline – on VKA)*	*Visit 2 (1 month into NOAC)*	*Visit 3 (2 months into NOAC)*	*Visit 4 (1 year into NOAC)*
Full medical and drug history obtained, including calculation of ^a^CHADS_2_ [44], ^a^CHA_2_DS_2_VASc [14], HASBLED [45], the Medication Related Complexity Index (MRCI) [46], SAMe-TT_2_R_2_ [26], the Charlson index [47] and whether the patient has symptomatic disease or not	Patient reviewed clinically	Patient reviewed clinically	IPQ/BMQ (NOAC)/ACTS instruments administered
Socio-demographic information^b^	Patient self-reported missed doses recorded + pill count	Patient self-reported missed doses recorded + pill count	PTS assessment if DVT patient
Informed written consent	Another 1 month prescription of NOAC given to patient	Another 1 month prescription of NOAC given to patient	Adherence assessment through GP summary care record, patient self-report and the 8-item Morisky Medication Adherence Scale
IPQ/BMQ (warfarin)/ACTS instruments administered	Bloods for UEs/FBC	Bloods for UEs/FBC (if not done at visit 2)	
Patient switched to NOAC (1 month prescription)	IPQ/BMQ (NOAC)/ACTS instruments administered	Patient transferred to GP for on-going prescriptions	
PTS assessment if DVT patient	PTS assessment if DVT patient	PTS assessment if DVT patient	

^a^only for patients prescribed anticoagulant therapy in the context of atrial fibrillation

^b^socio-demographic information will be obtained from the patient’s medical notes, namely age, gender, post-code, ethnicity

For studies II and III, patients will be reviewed by pharmacists trained in the field of anticoagulation working at King’s College Hospital. The questionnaire will be administered by the pharmacist reviewing the patient in clinic, with patients offered the option of completing the questionnaire in clinic or taking home and returning at their subsequent clinic visit. Patients will be advised that the questionnaires will take approximately 20 min to complete.

Patients who are prescribed long-term anticoagulation for the secondary prevention of VTE, and whose primary VTE event was a deep vein thrombosis, will at each clinic visit, have an assessment of post-thrombotic syndrome (PTS) using the Villalta score [39], as part of their clinical review at clinic visits.

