#### Study II

Following completion of the psychometric instruments, patients in group 2 (from study I) will be asked if they wish to switch to a NOAC, according to local guidelines. Patients who then switch will prospectively be followed in clinic will be required to return for a clinic visit at 1, 2 months and 1 year into NOAC treatment allowing for the longitudinal assessment of adherence. At their 1-month follow-up visit (visit 2), patients will be given a questionnaire pack comprising of validated instruments designed to assess their newly established beliefs about NOAC therapy and any short-term changes in quality of life. The same instruments will be administered at their 1-year follow-up (visit 4) to determine whether any changes in beliefs, illness perceptions and quality of life are sustained. The questionnaire pack will be posted to the patient, prior to their clinic visit 4, requesting them to complete and bring along to their clinic appointment. To prevent participant burden, no questionnaires will be administered at the 2-month follow-up visit (visit 3). However, at 1-month and 2-month follow-up visits (visits 2 and 3), patients will be asked to bring in their NOAC medication to clinic, so a pill count can be conducted by the reviewing clinician.

Patients identified in this group who decline a switch to a novel agent, will also be followed longitudinally for the duration of the study and any clinically relevant outcomes will be reported. Furthermore, their reasons for not wishing to switch, will formally be recorded and described.

Analysis for studies I and II will be conducted on an intention to treat basis.

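### The take-home option for questionnaires does not except visit 1, so a switcher's warfarin baseline can be completed up to about a month after starting the NOAC, contrary to the order stated for Study II

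*Protocol article*

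**What the plan says.** Three parts of the protocol article bear on when the baseline questionnaire is completed.

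- **Study II section.** The order is fixed: "Following completion of the psychometric instruments, patients in group 2 (from study I) will be asked if they wish to switch to a NOAC". Switchers are then "required to return for a clinic visit at 1, 2 months and 1 year into NOAC treatment".
- **Table 1 (schedule for studies II and III).** The first column is headed "Visit 1 (baseline – on VKA)". It contains both "IPQ/BMQ (warfarin)/ACTS instruments administered" and "Patient switched to NOAC (1 month prescription)". The next column is "Visit 2 (1 month into NOAC)", where the IPQ, the NOAC version of the BMQ and the ACTS are given.
- **Text below Table 1.** For studies II and III the reviewing pharmacist administers the questionnaire, "with patients offered the option of completing the questionnaire in clinic or taking home and returning at their subsequent clinic visit". No visit is named and none is excepted.

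For the one-year visit the Study II section sets a separate procedure: "The questionnaire pack will be posted to the patient, prior to their clinic visit 4". No questionnaire is given at the two-month visit.

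**The concern.** The visit 1 scores are meant to describe the patient on warfarin. They are the reference for three of the five listed outcomes: change in beliefs, in illness perceptions and in anticoagulation-specific quality of life, each at one month and one year after the switch. Hypotheses 5 and 6 rest on two of these changes. The same scores are group 2's data for Study I, where they are compared with group 1, whose patients answer by post and stay on warfarin. Group 3 follows the same schedule, so its baseline is exposed in the same way.

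A pack completed on the NOAC is no longer a warfarin baseline in the sense that Table 1 intends. Patients choose for themselves whether to take the pack home, so any subset with late baselines is self-selected. A true pre-switch score cannot be recovered once the patient has switched.

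**Working it through.** **1. Which visits can the take-home option concern?**

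| Visit | Questionnaire? | Can the option apply? |
|---|---|---|
| 1 (on warfarin; switch made here) | Yes | Yes, not excepted |
| 2 (1 month into NOAC) | Yes | Yes |
| 3 (2 months into NOAC) | None | No |
| 4 (1 year into NOAC) | Yes, posted before the visit | No, separate procedure |

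Only visits 1 and 2 remain.

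**2. How late can a pack be?**

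- Visit 1 pack: the switch is at visit 1 and the next visit is 1 month into NOAC, so the pack can come back about 1 month after the switch. This is a maximum, because completion may come well before return.
- Visit 2 pack: the next visit is visit 3, so a pack counted as the one-month score can come back at 2 months.

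**3. Can the statements all hold?** For a switcher who takes the visit 1 pack home, no. The Study II section requires completion before the switch is offered. Table 1 has the switch made at that visit. The text below Table 1 allows return at the following one.

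**4. Size under an explicit assumption.** The documents give no take-home share and no completion dates, so this is an illustration only. Let m0, m1 and m12 be the true mean scores on warfarin, at one month and at one year. Let p be the share of switchers who complete the baseline after the switch. Assume that late forms already show the full one-month level and that late completers do not otherwise differ.

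- Observed baseline = (1 − p)·m0 + p·m1
- Observed one-month change = m1 − observed baseline = (1 − p)·(m1 − m0)
- Observed one-year change = (m12 − m0) − p·(m1 − m0)

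| p (assumed) | Share of the true one-month change that is observed |
|---|---|
| 10% | 90% |
| 20% | 80% |
| 40% | 60% |

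**5. Study I.** Only switchers can be affected. The sample size section assumes 30% refusal, so the share of group 2 with a late baseline is 0.70·p: 14% at p = 20% and 28% at p = 40%.

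The article states no figure on this point, so there is none to reproduce.

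**The case against.** The best defence is that the texts can be read together. The Study II section gives the specific rule for group 2 at visit 1, and the take-home sentence is general. On that reading, visit 1 packs are completed first and the option serves visit 2 only. The Study I section also places group 2's visit 1 questionnaire in Study I, while the take-home paragraph opens with studies II and III.

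Part of this stands: applying the option to visit 1 is an inference, because the sentence does not name that visit. The inference is sound, however. Table 1 is the schedule for studies II and III and begins with visit 1, no visit is excepted, and for group 3 visit 1 lies plainly inside Study III. Clinic staff following the text as written could hand out a take-home pack at visit 1.

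Other limits also stand:

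- **Direction.** A reader might infer that the bias always pulls change towards zero. The documents do not support that. The visit 1 BMQ asks about warfarin, so after the switch it becomes a retrospective rating. Contrast with the new drug could make warfarin look worse and enlarge the change.
- **Size.** A reader might take the (1 − p) factor as the expected loss. It needs every late form to show the full one-month change already. A pack that takes about 20 minutes may be completed on the day of the visit, with little effect.
- **Decliners.** A reader might extend the point to patients who refuse the switch. They have no NOAC experience to carry into a late form, and the Study II section says they are followed.
- **Reach.** The NOAC adherence and persistence outcomes do not use visit 1 scores, and the NOAC version of the BMQ is first given at visit 2.
- **Missing detail.** Completion dates and visit windows may be in the full protocol or on the study form. Their absence from the article is not part of the finding.

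**Conclusion.** The point holds as a conflict between two stated rules. Followed as written, the take-home option allows a baseline labelled as on warfarin to be completed on the NOAC, at most about a month after the switch. It concerns only patients who both switch and take the visit 1 pack home.

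For those patients it can bias the three change outcomes (and so hypotheses 5 and 6), group 2's warfarin data in Study I, and group 3's baseline. Neither direction nor size can be determined from the documents. The proportional losses shown above are a worst case for attenuation and rest on assumed values of p.

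The documents do not show that any baseline was in fact completed late, and they do not support a claim that baselines are invalid in general. The case for correction is that the ambiguity is cheap to remove and a lost pre-switch measurement cannot be replaced.

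**What to change.** 1. **Reconcile the Study II and Data collection sections.** State that the take-home option does not apply at visit 1. For groups 2 and 3 the IPQ, BMQ (warfarin) and ACTS are completed and handed in at the clinic, after written consent and before the switch is discussed. Cost: one sentence in the protocol and about 20 minutes of clinic time per patient. Some patients who would have taken the pack home may leave it incomplete. Posting the pack before visit 1 is less suitable, because group 2 gives written consent at that visit, so study data would be collected before consent. Visit 4 differs in that patients are already enrolled.
2. **Record the completion date on every pack**, so that visit 2 packs completed or returned nearer two months can be identified and not taken as one-month scores without notice. Cost: one field on the form.
3. **For patients already enrolled** (recruitment began in July 2014), keep the baseline packs in the main analysis. Add a sensitivity analysis without those known to have been completed or returned after the switch. Outright exclusion is debatable, since it would remove a self-selected subset, and it may be impossible where packs carry no date. Apply the same sensitivity analysis to the group 2 versus group 3 comparison: if the rule is tightened partway, the two groups' baselines would have been collected under different rules.

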### Adherence to NOAC

During the first 2 months of therapy, adherence to NOAC will be recorded through a pill count at the 1 and 2 month follow-up visits (visits 2 and 3). This pill count will be conducted by the pharmacist reviewing the patient in clinic and will compare the number of tablets the patient has to the number of tablets the patient is expected to have, following the commencement of NOAC. When patients are reviewed in clinic at 1 year into their NOAC therapy, specific adherence screening questions will be asked to assess adherence during months 4 to 12 of NOAC therapy [40] in addition to asking patients how many doses of their anticoagulation they have missed during the last week. The adherence screening questions at this visit are informed from the 8-item Morisky Medication Adherence Scale [41]. Furthermore, in order to assess persistence with their anticoagulation therapy, patient’s summary care record and prescriptions records will be reviewed, allowing anticoagulation coverage to be calculated, during the period which the GP was prescribing the NOAC for the patient, in order to measure persistence up to this time point.

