#### Study III

Three hundred forty-two patients will be recruited into group 2 which will act as the control group. Power calculations (GPower 3.1) assuming one-tailed analysis using an independent groups design, suggest that a 1:1 matching i.e. recruiting 342 patients into the intervention group (group 3) would allow for the detection of a small-sized effect of the intervention (d = 0.20).

The Switching study has been reviewed and given a favorable opinion by the London-Dulwich Research Ethics Committee: REC reference: 13/LO/1468.

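### Study III takes self-reported adherence in clinic, and pill counts from reviewing pharmacists who will know which patients are on the pathway, so reporting bias could favour the pathway group

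*Protocol article*

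**What the plan says.** Under Study III, group 3 is an independent group with TTR below 50%, recruited after the pathway has been designed from group 2 data. It has the same clinic schedule as group 2. The two groups are compared on beliefs, illness perceptions, quality of life and adherence, in order to judge the pathway's effectiveness.

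Adherence is measured as follows:

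- **Months 1 and 2 (visits 2 and 3).** Patients bring in their tablets, and "This pill count will be conducted by the pharmacist reviewing the patient in clinic". Table 1 has self-reported missed doses recorded at the same visits.
- **One year (visit 4).** "When patients are reviewed in clinic at 1 year into their NOAC therapy, specific adherence screening questions will be asked"; these are based on the Morisky scale, and patients are also asked about doses missed in the last week.
- **Records.** Summary care and prescription records are reviewed to calculate coverage while the GP prescribes. The section Adherence to NOAC calls this persistence; Table 1 lists the GP record under adherence assessment at visit 4.

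On who does this, Data collection states: "For studies II and III, patients will be reviewed by pharmacists trained in the field of anticoagulation working at King’s College Hospital". Under Consent, confidentiality and data storage, the pharmacist also recruits and takes consent from group 2 patients, and group 3 follows a similar process. No masked or independent assessor is described.

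The Study III sample size rests on a calculation "assuming one-tailed analysis using an independent groups design", and says that 342 per group "would allow for the detection of a small-sized effect of the intervention (d = 0.20").

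**The concern.** The pathway cannot exist until group 2 data have been analysed, so the pharmacist who recruits and reviews a group 3 patient will know that the patient is on it. The protocol does not say this in words; it follows from the sequence of the studies and from the pharmacists' role.

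The Background gives the purpose of such a pathway as supporting adherence. Patients given that support may under-report missed doses to clinic staff, whatever they actually take, and a pharmacist who knows the group may probe or count differently. Either would make group 3 look better without any change in behaviour. Using the same method in both groups removes only the part of the bias that is common to both; the part linked to the pathway stays in the comparison. The power calculation is one-tailed, in the direction of benefit, which is also the direction in which this bias would be expected to run.

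At stake is whether a modest difference in interviewed adherence can be read as an effect of the pathway.

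**Working it through.** **Inputs from the protocol.** 342 per group; one-tailed, independent groups; d = 0.20 (Study III sample size). 30% refusal of the switch (Study I & II sample size).

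**Assumptions.** Neither alpha nor power is stated: one-sided 5% is used, with 2.5% as an alternative. The same refusal rate is assumed in group 3. The size of any bias, b (in SD units of the outcome), is not given in the protocol, so a range from 0.05 to 0.20 is shown.

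**Step 1: reproduce the plan's figure.** Power = Φ(d·√(n/2) − 1.645) = Φ(0.20 × √171 − 1.645) = Φ(2.615 − 1.645) = Φ(0.970) = 83%. The statement that 342 per group can detect d = 0.20 therefore holds at a one-sided 5% level.

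**Step 2: patients with NOAC adherence to measure.** 342 × 0.70 = 239.4, about 240 per group.

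**Step 3: smallest observed difference that is significant.** 1.645 × √(2/342) = 0.126 SD; with 240 per group, 1.645 × √(2/240) = 0.150 SD.

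**Step 4: false-positive rate with no true effect and a differential bias b.** Rate = Φ(b·√(n/2) − 1.645). For b = 0.10: at n = 342, Φ(1.308 − 1.645) = Φ(−0.337) = 37%; at n = 240, Φ(1.095 − 1.645) = Φ(−0.549) = 29%.

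| Bias b (SD) | 342 per group | 240 per group |
|---|---|---|
| 0 | 5% | 5% |
| 0.05 | 16% | 14% |
| 0.10 | 37% | 29% |
| 0.15 | 62% | 50% |
| 0.20 | 83% | 71% |

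At a one-sided 2.5% level and b = 0.10, the rates are Φ(1.308 − 1.960) = 26% and Φ(1.095 − 1.960) = 19%.

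**Step 5: what 0.1 SD means.** The protocol gives no SD for percentage adherence. For an assumed SD of 5 to 20 percentage points, 0.1 SD is 0.5 to 2 points.

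The bottom row needs care. A bias set equal to 0.20 SD is declared significant exactly as often as a true effect of that size, so 83% is the power from Step 1 restated. The table shows how sensitive the test is to a given bias, not how large the bias is.

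**The case against.** The case against is substantial, and most of it stands as a limit on the point.

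- **A measure free of this bias is already planned.** The 1-year record review does not depend on the interview. That stands. It shows supply rather than tablets taken, covers only the GP prescribing period, and is described mainly as persistence, which Study outcomes lists separately from adherence. It therefore does not make the self-report sound.
- **Pill counts are not the listed outcome.** Study outcomes places percentage adherence at 1 year, whereas the counts are at months 1 and 2. They cannot bias the 1-year result directly. They matter only so far as the general adherence comparison in Study III uses them.
- **Part of the mechanism is common to both groups.** Patients in both are told to bring their tablets and are seen by the same kind of pharmacist. Only a differential part counts, and the pathway's content and who delivers it are not yet stated.
- **Self-completion is not a full cure.** A patient who has received adherence support can over-report on paper too. Recruitment began in July 2014, so some group 2 interviews may already be done, and changing the mode for group 3 alone would add a bias of its own.

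A reader might go further and infer that this bias is likely to produce the whole d = 0.20 effect sought on adherence. The protocol does not support that. It attaches d = 0.20 to no named outcome, Study III compares four kinds of outcome, and neither a bias size nor an adherence SD is given.

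**Conclusion.** The point holds in a limited form. The self-reported part of 1-year adherence and the early pill counts are unmasked, and they are obtained in a clinic whose pharmacists will know who is on the pathway. A bias that differs between groups 2 and 3 is plausible, would be expected to favour the pathway, and is not removed by using one method in both groups. The one-tailed test is sensitive to it: 0.1 SD would take an assumed 5% error rate to about 37% at 342 per group, or 29% at about 240.

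Those percentages are illustrative. They rest on the assumed alpha, on the same refusal rate in both groups, and on a bias size chosen for the example. The record-based coverage is unaffected and partly protects the 1-year conclusion. It need not replace self-report as the lead measure, since supply and adherence are different quantities and the plan keeps persistence separate.

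**What to change.** 1. For groups 2 and 3 alike, add the Morisky-based items and the last-week missed-dose question to the pack that Study II already posts before visit 4. Have them self-completed and returned sealed to the research team, not opened by the reviewing pharmacist. Group 1 already returns its questionnaires to the research team in a pre-paid envelope, so the route exists.
2. Report the Study III self-report comparison side by side with the record-based coverage already planned, computed by the same rule in both groups.
3. Describe the month 1 and 2 pill counts as unmasked and supportive.
4. If some group 2 visit 4 interviews are already complete, record the mode of collection for every patient. Do not compare interviewed answers in group 2 with self-completed answers in group 3 without a sensitivity analysis for mode.

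The cost is about one extra page in an existing pack and a few sentences in the plan, with no extra staff. The downside is some unanswered items, and self-completion reduces desirability bias without removing it.
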